## Abstract

**Background:**

The traditional system of routine outpatient follow-up of chronic disease in secondary care may involve a waste of resources if patients are well. The use of patient-reported outcomes (PRO) could support more flexible, cost-saving follow-up activities. *AmbuFlex* is a PRO system used in outpatient follow-up in the Central Denmark Region. PRO questionnaires are sent to patients at fixed intervals. The clinicians use the PRO data to decide whether a patient needs a visit or not (standard telePRO). PRO may make patients become more involved in their own care pathway, which may improve their self-management. Better self-management may also be achieved by letting patients initiate contact. The aim of this study is to obtain data on the effects of patient-initiated follow-up (open access telePRO) on resource utilisation, quality of care, and the patient perspective.

**Methods:**

The study is a pragmatic, randomised, controlled trial in outpatients with epilepsy. Participants are randomly assigned to one of two follow-up activities: a) standard telePRO or b) open access telePRO. Inclusion criteria are age ≥ 15 years and previous referral to standard telePRO follow-up at Aarhus University Hospital, Denmark. Furthermore, patients must have answered the last questionnaire via the Internet. The number of contacts will be used as the primary outcome measure. Secondary outcome measures include well-being (WHO-5 Well-Being Index), general health, number of seizures, treatment side effects, mortality, health literacy (Health Literacy Questionnaire), self-efficacy (General Self-Efficacy scale), patient activation, confidence, safety, and satisfaction. In addition, the patient perspective will be explored by qualitative methods. Data will be collected at baseline and 18 month after randomisation. Inclusion of patients in the study started in January 2016. Statistical analysis will be performed on an intention-to-treat and per-protocol basis. For qualitative data, the interpretive description strategy will be used.

**Discussion:**

The benefits and possible drawbacks of the PRO-based open access approach will be evaluated. The present study will provide important knowledge to guide future telePRO interventions in relation to effect on resource utilisation, quality of care, and the patient perspective.

**Trial registration:**

ClinicalTrials.gov: NCT02673580 (Registration date January 28, 2016)

**Electronic supplementary material:**

The online version of this article (doi:10.1186/s12913-017-2015-8) contains supplementary material, which is available to authorized users.

## Background

The Danish health care system is changing from inpatient towards a greater outpatient activity. From 2002 to 2009, there was a 50% increase in outpatient activity in Denmark, primarily related to the number of contacts per patient [1]. At the same time, there appears to be a growing need of health care services especially for the growing group of patients with chronic diseases and an increased focus on patient involvement. The challenge is to manage this without compromise on quality of care and patient outcomes. Follow-up visits for patients with chronic diseases in secondary care are traditionally based on regular pre-booked visits, which may be arranged when the patient is well. Thus patients as well as clinicians may find such visits unnecessary. The volume of appointments leads to capacity issues in outpatient clinics that struggle to respond rapidly to patients’ requests for help [2].

One way of handling this challenge may be to let patients report essential information on health status and symptoms from home before or instead of visiting the outpatient clinic. Patients’ own reports on health condition are termed patient-reported outcomes (PRO). The American Food and Drug Agency definition of PRO, *“A measurement based on a report that comes directly from the patient about the status of a patient’s health condition without interpretation of the patient’s response by a clinician or anyone else”* [3], focuses on the source of information and points out the importance of the patient perspective. The use of PRO in clinical practice is becoming increasingly common, and studies have reported improved patient-clinician communication, more effective self-management, and better utilisation of resources when PROs are used, whereas findings related to effects on patient outcomes are less consistent [4–7].

PRO may facilitate patient involvement because the problems reported as important by the patient are taken into consideration in the decision-making process [8–10]. However, patient involvement is not a goal in itself but rather a means to increase the patient’s self-management. Self-management refers to the individual’s ability to manage symptoms, treatment, physical and psychosocial consequences, and life style changes inherent in life with a chronic disease [11]. In practice, PRO is supposed to promotes a patient-centred dialogue between the patient and the clinicians in which the patient’s view and opinion on his health are included. Thus, implementing PRO into clinical practice allows patients to actively participate in their own care, by which their self-management may improve [8].

*AmbuFlex* is a generic clinical PRO system which is not limited to specific patient groups, organisations or medical record systems [12]. As of December 2015, AmbuFlex had been implemented in nine patient groups at 15 outpatient clinics in Denmark [13]. An analysis initiated by the Danish government based on experiences with AmbuFlex has demonstrated a positive national business case and considerable quality gain [14]. The Danish government and Danish regions, who run the public hospitals, have decided on an agreement for nationwide implementation of PRO in three diagnostic group, including epilepsy, before 2020. AmbuFlex was implemented for epilepsy outpatients at Aarhus University Hospital in March 2012 and is now used at three neurological departments in the Central Denmark Region. As of August 2016, 4,513 epilepsy outpatients have been referred to AmbuFlex, which are about two-thirds of all epilepsy outpatients in the region. The PRO questionnaire used contains information on specific aspects of daily life with epilepsy and has been developed in close cooperation with clinicians and patients. Face validity is fundamental and has been ensured during the development of the questionnaire [12, 13]. A graphical PRO overview is presented to the clinicians, who use the PRO data for clinical decisions together with other available clinical data in the record to decide whether the patient needs a visit or not. If a PRO questionnaire is used to evaluate the patient’s need for a hospital visit, the PRO data must be obtained outside the hospital. This is called tele-patient-reported outcome (telePRO) [12]. Experiences from epilepsy outpatient clinics have shown that of 8,256 PRO-based contacts, 48% were handled without additional contact to the patient other than the PRO questionnaire [13]. A preliminary interview study has indicated that patients experience greater flexibility in care, the saving of time, improved communication with the clinicians, and increased knowledge about their own disease [13, 15].

The AmbuFlex method used at the three neurological departments is called *standard telePRO.* In standard telePRO, regular scheduled visits are replaced with fixed questionnaires at intervals similar to those of the former pre-booked visits. A patient-initiated approach “open access” telePRO has been developed in which patients have access to their own PRO data and are able to initiate contact with the clinic by filling in a PRO questionnaire. A review by Whear et al. investigated the effectiveness of patient-initiated clinics in chronic conditions in secondary care and included seven randomised trials. The review found that the risk of harm from using the patient-initiated clinic model is low in patients with breast cancer, inflammatory bowel disease, and rheumatoid arthritis. The included studies found few significant differences in clinical outcomes between traditional appointment scheduling and the patient-initiated follow-up method. In four of the studies, the patient-initiated model was associated with savings in clinician time and resource use [2]. A review by Taneja et al. that included five of the same randomised studies reached the same conclusion [16], while another review showed no significant differences in psychological and health-related quality of life outcomes between consultant-led and patient-initiated clinics. Patients have reported better satisfaction in patient-initiated clinics compared to usual care [17]. The patient-initiated method used was broadly the same in the studies included in the three reviews. Patients could request clinical advice by calling the clinic and, if necessary, arranging an appointment to see a clinician. However, none of the included studies used PRO as the main access point in the open access intervention, and all studies contain methodological limitations [2, 16, 17].

### Objectives

The aim of this study is to provide insight into the effects of patient-initiated telePRO follow-up. The specific aims are to compare resource utilisation, quality of care, and the patient perspective of two outpatient follow-up activities: a) standard telePRO (fixed-interval telePRO follow-up) and b) open access telePRO (patient-initiated telePRO follow-up). We hypothesise that 1. Number of contacts is less in open access telePRO, 2. Quality of care in open access telePRO is at least as good as in standard telePRO, and 3. Patient self-management and experiences in open access telePRO are better than standard telePRO.

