### Outcomes

The effects of patient-initiated follow-up (open access telePRO) will be evaluated with regard to three different aspects: resource utilisation, quality of care, and the patient perspective. Resource utilisation will constitute the primary outcome, measured by number of contacts. Quality of care and the patient perspective constitute the secondary outcomes. Quality of care includes pivotal clinical quality measures (mortality, seizure, and treatment side effects) as well as more general patient-oriented quality measures (well-being and general health). The patient perspective includes measures related to self-management, such as health literacy, self-efficacy, and patient activation. Measures of confidence, safety, and satisfaction will be used to describe patient experiences. The patient perspective is primarily explored by qualitative methods in a complementary PhD study. An overview of primary and secondary outcomes, data sources, and measurement timeline is shown in Table 1.

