### Analyses

Descriptive statistics will be used to describe differences in the baseline characteristics of participating patients in the two arms of the trial. Statistical analysis will be intention to treat, whereby all randomised participants will be included in the analysis according to their randomised allocation. The primary outcome, total *number of contacts* in the two arms*,* will be analysed using a sample t-test. If the distribution of data is skewed, we will use medians and nonparametric tests. For secondary outcomes, a chi-square test or logistic regression will be used for dichotomous outcome data and sample *t*-test or multiple linear regression analysis will be used for continuous outcome data. Non-parametric tests will be used if continuous data are not normally distributed. Demographics covariates (sex, age, education, marital status, and epilepsy diagnosis duration) will be included in the per- protocol analysis.

For qualitative data, ID will be employed as the overriding research approach. ID is an inductive research strategy in which constant comparative method with concurrent data collection and analysis is utilised to gain a deeper insight and understanding of human experiences within their natural context. The result is a comprehensive interpretation, potentially a *model of explanation* of the phenomenon under study, which can provide clinical practice with a research-based choice of action [31]. ID is considered appropriate in the present study because the approach is suited for exploration of specific clinical issues, in this case how patients with epilepsy experience standard and open access telePRO follow-up.

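### Hypothesis 2 is a non-inferiority-type claim on quality of care, but it is given the same difference tests as the superiority hypotheses, with no margin or confidence-limit rule

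*Protocol article*

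**What the plan says.** Objectives in the protocol article sets out three hypotheses with three directions. Contacts are expected to be fewer under open access. For quality of care the claim is that "Quality of care in open access telePRO is at least as good as in standard telePRO". For the patient perspective it is that "Patient self-management and experiences in open access telePRO are better than standard telePRO".

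Outcomes places mortality, seizures, side effects, well-being and general health under quality of care, calls the first three pivotal, and makes all of them secondary.

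Analyses then treats the secondary outcomes as one group: "For secondary outcomes, a chi-square test or logistic regression will be used for dichotomous outcome data", a t-test or multiple linear regression for continuous data, and "Non-parametric tests will be used if continuous data are not normally distributed". On the analysis set it says: "Statistical analysis will be intention to treat, whereby all randomised participants will be included in the analysis according to their randomised allocation". The Abstract adds a per-protocol analysis, and Analyses mentions one with demographic covariates. Neither place links it to a particular hypothesis.

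Sample size powers the number of contacts only.

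**The concern.** The authors separate *at least as good* from *better*, so hypothesis 2 is a claim that open access is not materially worse. A test of no difference can support such a claim only if open access turns out superior. A non-significant result leaves open any deficit inside the confidence interval, and without a margin nobody can say whether that deficit matters.

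The Discussion expects only small differences between two rather similar forms of follow-up, so non-significant quality results are a likely outcome. Fewer contacts are of practical value only if quality is kept up, and the Background frames the task as managing demand without loss of quality. What the trial may conclude about quality therefore bears on how its main result is used.

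**Working it through.** **The plan's own figure.** Inputs from Sample size: SDs 2.38 and 3.41, difference 1, power 90%, p 0.05 (taken as two-sided), ratio 0.8.

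- Normal approximation with SD 3.41 in the smaller arm: (2.38² + 3.41²/0.8) × (1.960 + 1.282)² = 212.2 in the larger arm, and 0.8 × 212.2 = 169.8 in the smaller.
- The unequal-variance t calculation moves this to 214 and 172, with power 90.1%, so the stated numbers are reproduced.
- With the SDs attached to the arms as labelled (3.41 in open access, n = 214), power is 92.2%. The stated size is then slightly generous. That is a separate matter and does not affect this point.

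No corresponding figure exists for hypothesis 2.

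**Precision for a continuous quality outcome, in SD units (no SD needs to be assumed).**

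- SE = √(1/172 + 1/214) = 0.1024 SD.
- 95% CI half-width = 1.96 × 0.1024 = 0.20 SD.

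**Chance that a two-sided 5% test is non-significant when open access is truly worse by d**, approximately Φ(1.96 − d/0.1024):

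| True deficit | P(non-significant) |
|---|---|
| 0.1 SD | 84% |
| 0.2 SD | 50% |
| 0.3 SD | 17% |

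**Binary outcome.** The article gives no event rates, so these are assumed. The half-width is 1.96 × √(p(1−p)) × 0.1024, which is about 6, 8 and 9 percentage points for rates of 10%, 20% and 30%. Observed deficits up to roughly those sizes would be non-significant.

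**Margin that 172/214 could support.** With one-sided 0.025, 90% power and a true difference of zero: (1.960 + 1.282) × 0.1024 = 0.33 SD. On WHO-5 rescaled to 0–100:

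| Assumed SD | Margin at 90% power |
|---|---|
| 15 | 5.0 points |
| 20 | 6.6 points |
| 25 | 8.3 points |

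Power at 172/214 for tighter margins is 83% at 0.3 SD, 69% at 0.25 SD and 50% at 0.2 SD.

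**Dilution under intention to treat.** Randomisation says that open-access patients who decline stay on standard telePRO, and the 0.55/0.45 allocation shows that some refusal is expected. Ethics says that patients who do not respond within twice their interval are reallocated to standard telePRO. With 3- or 6-month intervals that falls at 6 or 12 months, inside the 18-month follow-up. With a 12-month interval it falls at 24 months, outside it.

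The article gives no refusal rate. If a fraction c takes up open access and refusers are unaffected, a 0.2 SD deficit among takers appears as 0.2c:

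| Assumed uptake c | Deficit seen | P(non-significant) |
|---|---|---|
| 90% | 0.18 SD | 58% |
| 80% | 0.16 SD | 65% |
| 70% | 0.14 SD | 72% |

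A complier estimate undoes the dilution, but its SE grows roughly as 1/c. At an assumed 80% uptake the 90%-power margin becomes 0.332/0.8 = 0.41 SD, or about 8.3 points at SD 20.

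**The case against.** The strongest reply is that a reader might infer that the plan will take p>0.05 as proof of equal quality, and the article does not say this. It gives no rule for reading a non-significant secondary result, and it states its aim as comparison and insight. That part of the objection stands: the fault is a missing decision rule, not a declared misreading.

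A reader might also infer that none of the named methods could ever serve hypothesis 2. That goes too far. The t-test and the two regressions yield estimates and confidence intervals that could be set against a margin. Only the margin and the rule are absent.

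Nor is intention to treat the only analysis planned. A per-protocol analysis is named, though not for this hypothesis.

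It can further be said that quality of care is secondary, and that an analysis plan not shown may hold a margin. This carries less weight. The article itself prints both the hypothesis and the tests, and the two do not fit.

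Finally, it is tempting to say that a non-inferiority test would come free, because 225/275 gives 90% power for a margin of 5.8 points at SD 20 (3.24 × 20 × √(1/225 + 1/275)). That assumes all 500 recruits give 18-month data, whereas Sample size sets 500 to allow for attrition. At 172/214 the figure is 6.6 points.

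**Conclusion.** The point holds as a mismatch between a stated hypothesis and its stated analysis. As written, hypothesis 2 can be supported only by a superiority finding, and a non-significant result says little: about half of trials this size would miss a true 0.2 SD deficit, and more would if some patients decline open access. The figures in SD units rest on 172/214 analysed patients, a normal approximation and no baseline adjustment. Adjustment would sharpen them somewhat. The WHO-5 SD, the event rates and the uptake fractions are assumptions shown as ranges.

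The comparison of contacts, the sample size and the conduct of the trial are untouched. The plan should be fixed on this point, but it is not a fault that invalidates the trial. Which outcome should lead and how wide the margin should be are open to clinical debate.

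**What to change.** In Analyses, state for each quality-of-care outcome that the between-arm difference will be reported with a 95% confidence interval, adjusted for baseline where baseline is measured, in both the intention-to-treat set and the per-protocol or complier set. Add that p>0.05 will not be taken as support for hypothesis 2. A complier estimate is preferable to simply dropping refusers, because control patients are not offered open access and so cannot be sorted in the same way.

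Then choose one of two routes:

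- **(a)** Before any follow-up data are seen, name one lead quality outcome, agree a clinical margin for it, and claim *at least as good* only if the confidence limit excludes that margin in both sets. Report the other outcomes by estimation, without that claim.
- **(b)** Reword hypothesis 2 as estimation, with no non-inferiority claim.

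Both routes cost only wording and, for (a), agreement on a margin. Under (a) the planned 172/214 gives 90% power only for a margin of about 0.33 SD, with less power in the complier analysis and for passing both sets together. A tighter margin would need more patients or lower power. The downside is that the claim may fail under (a) or has to be given up under (b).

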## Methods

The study follows the (Additional file 1: SPIRIT checklist): Standard protocol items for clinical trials [18].

### Design

This study is a pragmatic two-arm randomised controlled trial. Participants are randomly assigned to one of two follow-up activities: (a) standard telePRO or (b) open access teleRPO.

### Study population

Participants are epilepsy outpatients recruited from the epilepsy clinic at Aarhus University Hospital in Central Denmark Region, Denmark.

Inclusion criteriaAge ≥ 15 yearsDiagnosis or suspicion of epilepsy (IC-D 10 codes: G40, Z033a, DR568 and DR568E)Already referred to standard telePRO by a clinicianAble to answer the questionnaire via the Internet, indicated by having answered the last questionnaire via the Internet

Exclusion criterionReferred to telePRO follow-up with proxy questionnaire. Patients can be referred to a proxy questionnaire if they have cognitive problems and need help from a relative or health professionals.

### Intervention

#### Reference group – standard telePRO

AmbuFlex (standard telePRO) is used in three epilepsy outpatient clinics in Central Denmark Region. In standard telePRO, outpatient follow-up activity is determined by a clinician and patients receive a questionnaire at fixed intervals (3, 6, or 12 months). The questionnaire includes information about aspect of daily life with epilepsy such as seizures, symptoms, medication adherence, and social aspects. Responses are automatically processed according to a specific algorithm and given a “green”, “yellow”, or “red” status. A red status indicates that the patient needs or wishes contact with the clinic, a green status that the patient has no current need of attention, while a yellow status indicates that the patient may need to be seen in the clinic, but a clinician has to decide whether further contact is needed. The patient can always overrule a decision by requesting contact. They can choose two different contact forms in the questionnaire: telephone consultation or a face-to-face consultation at the clinic. Non-responders get three reminders and are contacted if do not respond. Clinicians keep track of incoming yellow and red responses, and non-responders, and this information is presented on a PRO alert list. The PRO overview (Fig. 1) is presented graphically to the clinician within the electronic health record system, and used as decision aid together with other available health record information to decide whether the patient needs a visit or not [13].

**Fig. 1 Fig1:**
[figure not shown]
Screen capture of the clinicians’ overview in epilepsy clinics accessed from the Electronic Health Record of Central Denmark Region [13]. The colour dots in the upper row indicate the result of the automated PRO algorithm (red: definite need of contact, yellow: possible need of contact, green: no need of contact). Note that the colours of the bars have different meanings. The bars indicate the severity of the symptoms reported by the patient. A red or orange bar indicates a self-reported problem, a yellow bar some problem, and a green bar indicates no problems. Note: Labels were translated from Danish

